## Methods

### Study design

A multicentre non-blinded superiority randomised controlled trial on VAC vs. ROD. Danish, as well as other European centres, will be invited to participate. The study protocol adheres to the guidelines determined in Standard Protocol Items: Recommendations for Interventional Trials (SPIRIT) (Additional file 2) [45].

The VACOR study will include two separate studies: VACOR-Main and VACOR-Microdialysis.

All centres must participate in the VACOR-Main study, with only Odense University Hospital participating in the VACOR-Microdialysis study. VACOR-Main will report on all primary and secondary outcomes; in VACOR-Microdialysis, a sub-study of 10 patients from each group will be included. A microdialysis catheter will be placed in the peritoneal cavity, and samples of the peritoneal fluid will be collected every 6th hour to measure the concentration of lactate, glucose, pyruvate, glycerol, cytokines (IL-1b, IL-6, IL-10, TNF-a) and metalloproteins (MMP9 and MMP8). The purpose is to investigate intraperitoneal metabolic changes and inflammatory responses in the two groups.

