### Randomisation

Patients are included by a surgical equipoise followed by patient information and consent after recovery. The on-call surgeon will contact the primary investigator from each site when a patient is scheduled for diagnostic laparoscopy or explorative laparotomy on suspicion of secondary peritonitis. Patients fulfilling the inclusion criteria will be randomised after consent has been obtained by the surgical equipoise (Fig. 1). This could occur before, during, or at the end of index laparotomy, disclosing a complete overview of all potential candidates. Most patients will be able to receive both treatments regardless of what arm they are allocated without changing the treatment regimen. However, there will be some exceptions where it is necessary to modify or change the surgical treatment, irrespective of the randomisation allocation. Centres that do not receive approval from their respective scientific ethics committee to include patients through a surgical equipoise must obtain informed and written consent before randomisation. Randomisation will be web-based via (REDCap ®) in blocks of 2, 4, and 6 stratified for centre and age above or below 65 years. The justifications for stratifying according to the centre are that there might be differences in the surgical treatment, preoperative optimisation, and postoperative treatment, both in the ward and intensive care unit (ICU), which might affect the outcome. The patients will be randomised to either abdominal closure with ROD or open abdomen with VAC according to transparent reporting of trials (CONSORT) (Fig. 2). The randomisation tool and eligibility criteria can be accessed through our website, www.vacor.sdu.dk.

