### Preoperative patient assessment

The patients are preoperatively assessed according to Sequential Organ Failure Assessment (SOFA) to determine the degree of organ dysfunction [46].

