### Postoperative patient assessment

Immediately after index operation, the surgeon fills out the baseline form containing patient characteristics, Charlson comorbidity index, aetiology and extent of the peritonitis, surgical procedure, Mannheims peritonitis index and classification of the OA according to Bjork's classification [48, 49]. Patients can be transferred postoperatively to the intensive care unit (ICU) or the ward at the discretion of the treating team. Upon arrival to either the ward or the ICU, Acute Physiology and Chronic Health Evaluation II (APACHE II) score must be obtained by the attending anaesthesiologist [46, 50]. SOFA-scoring and routine blood samples with CRP, bilirubin, creatinine, and platelets must be performed daily within the first seven days after index operation. Discharge from the ICU will be at the discretion of the attending intensivist and surgeon.

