#### Data collection and participant timeline

The pre- and perioperative assessment will consist of: baseline data (sex, age, surgery date, height, weight, body mass index, ASA score, WHO performance score, smoking, alcohol consumption, presence of comorbidities, previous abdominal surgeries, and steroid use). Data for surgical findings include aetiology of disease, anatomical location of intestinal perforation, degree of contamination, surgical treatment, method of abdominal wall closure, and suture material used for abdominal wall closure. Postoperative monitoring consists of SOFA, APACHE II, CRP, VAC treatment duration, unplanned VAC change, and the number of laparotomies in the ROD group. A patient record review will be performed at the follow-up after one month, three months, one year, and five years (Fig. 3). All data will be stored in REDCap®, hosted by the Odense Patient data Explorative Network (OPEN).

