#### Statistical analysis

Patient characteristics will be summarised with frequencies and proportions (for categorical variables) or with mean values ± standard deviation, median values, quartiles, and minimum and maximum values (for numerical variables). Categorical variables will be compared using a Fisher's exact test and continuous variables with a Wilcoxon rank-sum test.

The primary peritonitis-related complication outcome will be compared between intervention groups by the Chi-square test, reported as relative risk with a 95% CI. The CCI outcome will be compared by linear regression with bootstrapped standard errors reporting the mean difference with 95% confidence intervals.

The main analysis will be performed as a superiority analysis of VAC treatment against primary closure with ROD. In addition, a non-inferiority analysis with a margin of 5% will be reported for peritonitis-related complications as a secondary analysis.

A univariate analysis will be performed on the individual complication types (abscess, leakage, etc.) and complications as a whole (peritonitis-related complications and CCI). Fisher's exact or Chi-square test will be used to compare the treatments depending on the number of observations.

Adjusted analysis by logistic regression will be performed for complications as a whole and the individual complications as an outcome, adjusted for age, performance status, and comorbidity. The above analyses will also be performed as a subgroup analysis where patients with APACHE II score > 10 will be included. This evaluates VAC and ROD in the most seriously ill portion of the patient population.

The hospital healthcare utility and average treatment costs are compared between the treatment groups. The resource use will be reported as the mean difference with 95% confidence intervals (CI) compared by linear regression. In case of deviations from normality assumptions, bootstrapping with 1000 repetitions will be performed. Finally, the proportion of patients who experience radiological, acute operations will be compared by binomial regression estimating relative risk (RR) with 95% CI.

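### The APACHE II > 10 severity subgroup is defined by a score taken after randomisation and normally after the allocated closure, so the arm can influence who is in it

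*Protocol article*

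**What the plan says.** The protocol article, Statistical analysis, sets the subgroup: "The above analyses will also be performed as a subgroup analysis where patients with APACHE II score > 10 will be included". It gives the purpose in the next sentence: "This evaluates VAC and ROD in the most seriously ill portion of the patient population". No time point for the score is given there.

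The time point is given under Postoperative patient assessment: "Upon arrival to either the ward or the ICU, Acute Physiology and Chronic Health Evaluation II (APACHE II) score must be obtained". Data collection and participant timeline agrees and places the score after surgery: "Postoperative monitoring consists of SOFA, APACHE II, CRP, VAC treatment duration, unplanned VAC change". No other APACHE II measurement is described, and nothing says that the score is to be worked out from preoperative values.

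On the timing of randomisation, the Randomisation section says: "This could occur before, during, or at the end of index laparotomy". Study design describes the trial as "A multicentre non-blinded superiority randomised controlled trial on VAC vs. ROD". On where the patient goes after surgery, and so where the score is taken: "Patients can be transferred postoperatively to the intensive care unit (ICU) or the ward at the discretion of the treating team".

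A severity score is assessed before surgery, but it is a different one: "The patients are preoperatively assessed according to Sequential Organ Failure Assessment (SOFA) to determine the degree of organ dysfunction".

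**The concern.** A subgroup keeps the protection of randomisation if membership is settled before allocation, or by something that allocation cannot change. A score taken after the allocated closure meets neither condition. If the type of closure affects sedation, ventilation or the choice between ICU and ward at the end of the operation, and these affect the recorded score, then the same patient could fall above 10 in one arm and not in the other. The two arms of the subgroup would then differ in underlying severity even if treatment had no effect on complications.

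This subgroup is the article's stated way of looking at the most seriously ill patients. The Discussion concedes that patients enter irrespective of general condition, that some may be overtreated, and that it is unclear which patients benefit from VAC. Readers will look to this subgroup for an answer.

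**Working it through.** **Order of events**

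1. Randomisation: before, during or at the end of the index laparotomy (Randomisation).
2. Allocated closure, VAC or suture: at that operation (Interventions).
3. Transfer to ICU or ward, chosen by a treating team that is not blinded (Postoperative patient assessment; Study design).
4. APACHE II: on arrival there (Postoperative patient assessment).
5. Selection of patients with APACHE II > 10 (Statistical analysis).

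Step 4 always follows step 1 and normally follows step 2. The documents alone settle this.

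**Illustration of size**

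The plan has no figure to reproduce, so every input here is an assumption except the cut-off of 10.

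- Underlying score S is normal with mean 11 and SD 6.
- Risk is p(S) = 1/(1 + exp(−[logit(0.40) + 0.10 × (S − 11)])), the same in both arms, so there is no true effect.
- VAC adds d points to the recorded score and ROD adds none. A VAC patient enters the subgroup when S + d > 10, that is S > 10 − d.
- Share in the subgroup = 1 − Φ((10 − d − 11)/6).
- Subgroup risk = mean of p(S) over S > 10 − d.

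For ROD the share is 1 − Φ(−1/6) = 56.6% and the subgroup risk is 50.2%. For VAC (differences taken from unrounded risks):

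| Rise d under VAC | Share of VAC patients | VAC subgroup risk | Spurious VAC benefit (points) | Spurious RR |
|---|---|---|---|---|
| 0 | 56.6% | 50.2% | 0 | 1.00 |
| 0.5 | 59.9% | 49.5% | 0.7 | 0.99 |
| 1 | 63.1% | 48.8% | 1.4 | 0.97 |
| 2 | 69.1% | 47.5% | 2.7 | 0.95 |
| 3 | 74.8% | 46.3% | 3.8 | 0.92 |
| 4 | 79.8% | 45.3% | 4.9 | 0.90 |

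With a steeper gradient of 0.15 per point, a 3-point rise gives 5.6 points. If VAC lowered the score, the sign would reverse: at 0.10 per point, a 2-point fall gives a spurious VAC harm of 3.1 points.

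A separate simulation used score means of 10 to 14, SD 6, measurement noise of SD 2, log-odds 0.12 per point, overall risk about 34% and no true effect. The postoperative cut gave RRs of about 0.97 for a 1-point rise, 0.93 to 0.95 for 2 points and 0.91 to 0.93 for 3 points. Cutting on the pre-randomisation score gave an RR of 1.00 throughout.

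**Bias against precision**

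Take 340 less 5% drop-out: 340 × 0.95 / 2 = 161.5 per arm. With d = 3 the subgroup holds 161.5 × 0.748 ≈ 121 VAC and 161.5 × 0.566 ≈ 91 ROD patients. The standard error of the risk difference is √(0.463 × 0.537/121 + 0.502 × 0.498/91) ≈ 0.069, or about 7 points. The 3.8-point bias is about 0.55 standard errors. At d = 1 the 1.4-point bias is about 0.2.

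**The case against.** The strongest reply is that the score is taken soon after surgery and will largely reflect the patient's state beforehand, so any shift may be small or absent. No passage says that VAC patients are more often ventilated or sent to ICU, or how such states would enter the score. This stands as a limit on size. It does not restore a subgroup fixed before allocation.

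It is also fair that even a 3-point shift produces a bias well inside the subgroup's sampling error. That lowers the stakes, but unlike sampling error the bias does not shrink with more patients, and the subgroup's confidence interval would not reflect it.

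A reader might infer more than the documents support:

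- *That the planned returns to theatre about every 48 h raise the score.* They come after an on-arrival measurement and cannot affect it.
- *That the subgroup will favour VAC.* The direction is unknown, and a lower score under VAC would bias the other way.
- *That the plan is at fault for naming no treatment-by-severity interaction test.* That is commonly left to the analysis plan, which is not shown, so it is not part of this point.

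On the repair, the preoperative SOFA is not a ready-made substitute. It is assessed before surgery, but Data collection and participant timeline does not name it among the pre- and perioperative data, and no cut-off is given.

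**Conclusion.** The point holds in this form: the severity subgroup rests on a post-randomisation score that the arm can influence in a non-blinded trial, so its comparison is not fully protected by randomisation. That conclusion needs only the order of events. The size is not known from the documents. Under the assumptions above it runs from nothing to about 5 percentage points for rises of 0 to 4 points at a log-odds of 0.10 per point, and a fall in the score reverses the sign.

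The flat statement that the subgroup comparison is biased would go too far, because membership can be changed by the arm but is not shown to be. The damage is confined to the APACHE II subgroup analyses. The main intention-to-treat comparison, the sample size, the interim analyses and the full-population secondary outcomes do not depend on it. This should be fixed, but it does not threaten the trial's main result.

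**What to change.** Define the severity subgroup on a measure fixed before randomisation. The most practical candidate is the preoperative SOFA, after confirming that the preoperative value is recorded in the trial database. Fix the cut-off before any comparison by arm. The alternative is APACHE II computed only from pre-randomisation values, where these exist. If an analysis by the postoperative APACHE II is kept, label it exploratory and state that it conditions on a post-randomisation variable.

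The cost is mainly a change of wording if preoperative SOFA is in the database. The APACHE II alternative may need extra data collection, since preoperative components are not described as recorded. There are two drawbacks: the subgroup becomes less directly comparable with work that uses APACHE II > 10, and a SOFA cut-off has to be chosen and justified because the article gives none.

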**Fig. 2 Fig2:**
[figure not shown]
CONSORT flow diagram

In cases where the surgeon finds that the allocated treatment may be contraindicated or is judged to harm the patient, it will be left to the surgeon's discretion to choose the most appropriate treatment. In cases where the bowels are left stapled in discontinuity as a part of the damage control principle, the patient's fascia cannot be closed due to swelling or the presence of abdominal compartment VAC treatment may be applied irrespective of the randomisation. These patients remain in the trial for an intention-to-treat and per-protocol analysis. By excluding such patients, there might be a risk of selection bias. Any eligible patient not included will be registered in a screening log.

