The interim analysis will be performed at 25%, 50%, and 75% of recruited patients on the primary outcome after 30-days to detect significant differences between groups at the earliest possible time, ultimately leading to the termination of the study. We have adjusted our power calculation to the interim analyses using the O'Brien–Fleming method. The study group will have access to the results of the interim analyses and may make the final decision to terminate the study.

All of the above analyses will be performed as both intention-to-treat (patients will be analysed according to their randomisation group) and per-protocol analysis (what actually happened). The main analyses will be performed as complete case analyses. Multiple imputations will impute missing values in a supplementary analysis, including baseline characteristics as predictors.

*P* values < 0.05 will be considered statistically significant. Statistical calculations will be performed using Stata software (version 15, Stata Corp LP, Texas, USA).

In the VACOR-Microdialysis sub-study, the parameters will be compared using descriptive statistics for continuous and discrete variables. Repeated measurement across time points will be compared by mixed-effects regression models, including the interaction between time points and operation method and a random intercept for each patient. In addition, normality assumptions will be graphically assessed using quantile–quantile plots.

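### The per-protocol analysis is defined by treatment received: it is an as-treated comparison, probably biased against VAC, and intention-to-treat is not stated to be decisive

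*Protocol article*

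**What the plan says.** The Statistical analysis section sets two principles against each other. One is "intention-to-treat (patients will be analysed according to their randomisation group"). The other is the per-protocol analysis, explained only by the words in brackets: "and per-protocol analysis (what actually happened"). The scope is complete: "All of the above analyses will be performed as both intention-to-treat" and in this second way. The analyses listed above that sentence include the primary superiority comparison and a further one: "a non-inferiority analysis with a margin of 5% will be reported for peritonitis-related complications as a secondary analysis".

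The Randomisation section (text below Fig. 2) describes when treatment may depart from allocation. A general clause leaves the choice to the surgeon if the allocated treatment seems contraindicated or harmful. Specific situations follow: "In cases where the bowels are left stapled in discontinuity as a part of the damage control principle", or when the "fascia cannot be closed due to swelling or the presence of abdominal compartment". In these, "VAC treatment may be applied irrespective of the randomisation". On their handling: "These patients remain in the trial for an intention-to-treat and per-protocol analysis". The reason given is that excluding them could cause selection bias. The Discussion repeats that severe cases in which an open abdomen may be preferred are included under both principles.

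The adjusted logistic regression uses age, performance status and comorbidity.

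**The concern.** A per-protocol set normally contains patients treated as allocated and drops the others. Here the others stay in, and the only description of the grouping is what took place, in contrast to the randomised group. Read together, this is an as-treated analysis under a per-protocol name.

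The label matters because the regrouping is selective. Each specific trigger leads to VAC and signals a worse abdomen at the index operation. High-risk patients leave the ROD group and join the VAC group, which lowers the first rate and raises the second whatever VAC does. One trigger, abdominal compartment, also resembles a component of the primary endpoint in Table 1. The adjusted model does not repair this, since none of its covariates measures acute severity.

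The result would stand beside intention-to-treat for the primary question. The article calls superiority the main analysis, which ranks it above non-inferiority, but no sentence ranks intention-to-treat above the second analysis. If the two differ, the stated text does not say which one carries the conclusion.

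**Working it through.** **The plan's own figure.** The point does not rest on the sample size, but it was checked. For 40% vs 25%, two-sided 0.05 (sidedness assumed) and 80% power, 152 per arm are needed. An O'Brien–Fleming design with four equal looks inflates this by about 1.024, to 156 per arm. Division by 0.95 for drop-out gives 165 per arm, or 330 in total, about 3% below the stated 340. The stated figure is reproduced closely enough.

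**Inputs for the bias illustration.**
- From Sample size and power: 40% in ROD, 25% in VAC, 340 patients, taken as 170 per arm.
- Assumed, because the documents give neither: the share *f* of the ROD arm that switches to VAC (5–20%) and the complication risk *q* of those patients (60–80%).
- Simplification: no switching from VAC to closure.

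**Formulas.** With rates p_VAC and p_ROD by randomised arm:
- as-treated VAC rate = (p_VAC + f·q)/(1 + f)
- as-treated ROD rate = (p_ROD − f·q)/(1 − f)

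**One case in full, no true effect (40% in both arms).** Take f = 10% and q = 70%. Seventeen of 170 ROD patients switch, with 0.70 × 17 = 11.9 events, and each arm has 68 events.
- As-treated VAC: (68 + 11.9)/187 = 42.7%
- As-treated ROD: (68 − 11.9)/153 = 36.7%
- Spurious VAC excess: 6.1 points
- Switchers excluded instead: 40.0% − 36.7% = 3.3 points
- Intention-to-treat: 0 points

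Under no effect, with p the common rate, the as-treated excess simplifies to 2f(q − p)/(1 − f²) and the exclusion excess to f(q − p)/(1 − f). The ratio is 2/(1 + f), which is 1.8 at f = 10%. Regrouping switchers thus carries nearly twice the selection bias of dropping them, although the protocol keeps them in order to avoid that bias. Both excesses vanish if q = p.

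**Range.** The last column uses the planned 40% vs 25% by randomised arm, so the intention-to-treat difference is −15 points in every row.

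| f | q | VAC as-treated, no effect | ROD as-treated, no effect | Spurious excess (points) | As-treated VAC minus ROD, planned effect (points) |
|---|---|---|---|---|---|
| 5% | 60% | 41.0% | 38.9% | 2.0 | −12.3 |
| 5% | 70% | 41.4% | 38.4% | 3.0 | −11.3 |
| 5% | 80% | 41.9% | 37.9% | 4.0 | −10.3 |
| 10% | 60% | 41.8% | 37.8% | 4.0 | −9.6 |
| 10% | 70% | 42.7% | 36.7% | 6.1 | −7.6 |
| 10% | 80% | 43.6% | 35.6% | 8.1 | −5.6 |
| 20% | 60% | 43.3% | 35.0% | 8.3 | −4.2 |
| 20% | 70% | 45.0% | 32.5% | 12.5 | 0.0 |
| 20% | 80% | 46.7% | 30.0% | 16.7 | +4.2 |

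Under the planned effect, the benefit is attenuated in every row. It disappears or reverses only at 20% crossover with 70% risk or more.

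**The case against.** The best defence is that intention-to-treat on all randomised patients is planned and is untouched by the regrouping. The article is also a condensed text, and an exact per-protocol set or an order of precedence may sit in an analysis plan that is not shown. The second half has force: the lack of a precedence rule would not be a finding alone. But the bracketed gloss and the rule on keeping switchers are statements, not gaps, and together they fix an as-treated comparison.

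Other objections hold in part. The discretion clause applies to either arm, so switching is mainly, not strictly, from ROD to VAC. Greater severity among switchers is inferred from the listed reasons and the Discussion; the protocol does not state it. The repeated analyses include the adjusted model and the APACHE II > 10 subgroup, so the crude comparison is not the only one, but neither removes confounding by abdominal severity.

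Two stronger readings are tempting and are not supported:
- **That a 6-point bias breaches the 5% non-inferiority margin.** A margin is normally tested against a confidence limit. With 40% in both arms and 170 per arm, the 95% half-width is 1.96 × √(2 × 0.4 × 0.6/170) = 10.4 points. Non-inferiority would therefore usually fail under intention-to-treat as well, and the comparison shows no changed decision.
- **That the sample size is wrong because it ignores crossover.** The article gives only expected arm rates. The 40% comes from the on-demand arm of an earlier randomised trial and may already include departures from strategy. No crossover rate is documented.

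**Conclusion.** The point stands as a matter of definition and hierarchy. The analysis called per-protocol is as-treated. It is applied to every analysis, including primary superiority and non-inferiority, and intention-to-treat is not named as decisive. The comparison is confounded by indication, probably against VAC.

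Its size cannot be known from the documents. Under the assumed 5–20% crossover at 60–80% risk, the spurious VAC excess is about 2 to 17 points when there is no effect. Under the planned effect the apparent benefit shrinks. These figures assume equal arms, switching from ROD to VAC only, and switchers at higher than average risk.

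A reader might infer that the two analyses are bound to contradict each other. The working does not support that: at 5–10% crossover under the planned effect they agree in direction. They may conflict, and the article should say in advance which result governs. The intention-to-treat result is not biased by this regrouping.

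**What to change.** Change the wording in Statistical analysis, and match it in Randomisation and the Discussion:

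1. State that the superiority conclusion rests on intention-to-treat.
2. Define per-protocol as patients treated according to their allocation, and label it supportive. It still carries selection bias (3.3 points in the worked case), so it should not decide.
3. If a treatment-received analysis is kept, call it as-treated, label it exploratory, and adjust it for severity scores already collected: SOFA, APACHE II and the Mannheim peritonitis index. The preoperative SOFA is the cleanest, because APACHE II is scored on arrival at the ward or ICU, after the abdomen has been closed or left open.
4. Report the number of switches in each direction by arm, with reasons.

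A complier-average estimate with allocation as instrument is an optional sensitivity analysis. It needs its own assumptions (monotonicity and the exclusion restriction) and has a wider interval.

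The cost is protocol and analysis-plan wording. The severity scores and the method of abdominal closure are already recorded; the reason for each departure may need a field on the baseline form if it is not already there. No change to the sample size or to clinical management follows from this point.

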#### Sample size and power

With an expected peritonitis-related complications rate of 40% in the ROD group [20] and 25% in the VAC group [42, 44], the desired power of 80%, a significance level of 0.05, and an expected drop-out of 5%, a total of 340 patients should be included.

As the CCI distribution in this group of patients is unknown, we could not perform an explicit sample size calculation for this secondary outcome. A 0.32 standard deviation difference in mean CCI between the two groups could be detected with 80% power with this sample size.

To ensure sufficient recruitment, the study will be multicentre and European. Eight active centres have been included, and two are in process. Randomisation tools along with eligibility criteria are accessible through our website. The workflow and relevant contact details appear on posters at the participating departments. Study progress will be available on the website.

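### The stated P < 0.05 rule does not fit a final primary test that follows three O'Brien–Fleming interim looks, and interim results go to the study group of an unblinded trial

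*Protocol article*

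**What the plan says.** All references are to the Methods of the protocol article.

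- **Interim looks (Statistical analysis).** The primary outcome at 30 days is tested when 25%, 50% and 75% of patients have been recruited. The purpose is to find a significant difference early and end the study.
- **Adjustment (Statistical analysis).** "We have adjusted our power calculation to the interim analyses using the" O'Brien–Fleming method. No interim limit and no final nominal level is given.
- **Significance rule (Statistical analysis).** P "values < 0.05 will be considered statistically significant". The primary comparison is a chi-square test, with a relative risk and a 95% confidence interval.
- **Sample size (Sample size and power).** "With an expected peritonitis-related complications rate of 40% in the ROD group", 25% in the VAC group, and "a significance level of 0.05, and an expected drop-out of 5%, a total of 340 patients should be included".
- **Access and stopping (Statistical analysis).** "The study group will have access to the results of the interim analyses and may make the final decision to terminate the study".
- **Setting.** Study design describes the trial as non-blinded. Randomisation lets the surgeon depart from the allocated treatment when it is judged contraindicated or harmful. The section on relaparotomy on-demand leaves that decision to the treating surgeon.
- **Time points (Objectives).** The primary outcome is listed at 30 days, 90 days and one year.

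**The concern.** Adjusting a power calculation changes the number of patients. It does not change the significance level. Repeated efficacy tests use up part of the 5%, and under O'Brien–Fleming the final test must be a little stricter than 0.05 to pay for the earlier ones. The article names the method but states a significance rule and a confidence level that belong to a trial without interim tests. A final P between 0.043 and 0.05 would be positive under the stated rule and negative under the named method. That conflict falls on the main claim of the trial.

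The access rule raises a different risk. Treatment is not blinded, surgeons have discretion over departures from allocation and over relaparotomy, and several components of the primary outcome (Table 1) count only when an intervention was needed or when surgery confirmed them. Knowledge of an interim difference could affect who is enrolled, who departs from allocation and which events are recorded. With no stopping limit stated, the people who see the difference would also have discretion over whether it is large enough to stop.

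**Working it through.** **Inputs.** Event rates 40% and 25%, power 80%, significance level 0.05, drop-out 5%, total 340 (Sample size and power); looks at 25%, 50% and 75% plus a final analysis (Statistical analysis). Assumed, because not stated: a two-sided test, 1:1 allocation (consistent with blocks of 2, 4 and 6), and information proportional to recruitment.

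**1. The plan's own figure.** Per arm, n = [1.96·√(2·0.325·0.675) + 0.8416·√(0.40·0.60 + 0.25·0.75)]² / 0.15² = (1.298 + 0.550)² / 0.0225 ≈ 152. The total is 304, and 304/0.95 = 320. With a continuity correction it is 165 per arm, 330 in total, and 330/0.95 gives 348. A four-look O'Brien–Fleming design multiplies the size by 1.024:

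| Version | Before drop-out | After 5% drop-out |
|---|---|---|
| No continuity correction | 312 | 329 |
| Continuity correction | 338 | 356 |

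The stated 340 lies between these, so the sample size is not in dispute.

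**2. O'Brien–Fleming limits.** With four equally spaced looks, stop when |Z| ≥ C/√t, where t is the information fraction. C is chosen so that the overall two-sided error is 5%. Numerical integration over the joint distribution gives C = 2.024.

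| Information | Limit for abs(Z) | Nominal two-sided P | Cumulative error |
|---|---|---|---|
| 0.25 | 4.049 | 0.00005 | 0.005% |
| 0.50 | 2.863 | 0.0042 | 0.42% |
| 0.75 | 2.337 | 0.0194 | 2.09% |
| 1.00 | 2.024 | 0.0429 | 5.00% |

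**3. The stated rule at the end.** Keep the three interim limits and replace 2.024 by 1.96 (P < 0.05). The final look then adds 3.53% instead of 2.91%, so the total is 2.09% + 3.53% = 5.62%. With a Lan–DeMets O'Brien–Fleming-type spending function the total is 5.54%, and the correct final level is 0.0440. Simulating the chi-square test with 161 patients per arm and common event rates of 25%, 32.5% and 40% gives 5.5% to 5.7%.

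**4. A different final time point.** Step 3 requires the interim and final tests to use the same outcome. If the final test is at 90 days or one year, its correlation with the 30-day looks is weaker and the error rises above 5.6%. For one final test it cannot exceed the sum of the parts, 2.1% + 5% = 7.1%. A final level of 0.043 would not secure 5% in that case either, since the bound is 2.1% + 4.3% = 6.4%.

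**5. Power under the corrected limits.** Evaluable patients: 340 × 0.95 = 323. The expected final Z is 0.15/√(4·0.325·0.675/323) ≈ 2.88 with pooled variance, and group-sequential power is 81.2%. With unpooled variance it is 82.2%.

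**6. Access.** No arithmetic applies. The looks exist to detect a difference between groups, so their results are comparative. The article sends these results, and the termination decision, to the study group, and describes the trial as non-blinded.

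**The case against.** The strongest defence is that the 0.05 sentence is a general convention placed next to the software statement. It covers the baseline, individual-complication, subgroup and cost comparisons too, and was not written for the final primary test. A power calculation cannot be adjusted by O'Brien–Fleming without its critical values, so the authors may well have had a final level near 0.043 in mind, with "the desired power of 80%, a significance level of 0.05" as the overall error. Exact limits are also commonly left to an analysis plan. This stands as far as intent goes, and it is why the error figure is conditional. It does not remove the conflict: the article prints a rule and a 95% interval that contradict the method it names, and it makes no exception for the primary outcome.

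A reader might infer that 0.05 applies at all four looks, which would give an error of 12.6%. The document does not support that, because it would leave the O'Brien–Fleming sentence without meaning.

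A reader might also infer that the surgeons who recruit, override the allocation and decide on relaparotomy belong to the study group. The article does not define the group's membership. Overlap is plausible, but it is not stated. Nor does silence about an independent committee prove that none exists, since an article condenses its protocol. The point rests only on the access rule that is stated.

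**Conclusion.** The concern holds in a limited form. On the text as written, the significance rule for the primary outcome conflicts with the named sequential method. The size is modest: about 5.6% instead of 5% if O'Brien–Fleming limits govern the interim looks, the final test uses 0.05 and the 30-day outcome, and the looks fall at equal information steps. For a single final test at 90 days or one year, the error lies above 5.6% and at most at about 7.1%. The sample size is sound.

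The access rule is a separate weakness and is stated outright. It creates a risk of bias whose size cannot be calculated from the document. It does not show that bias will occur.

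**What to change.** **Significance level.**
- State that the general P < 0.05 rule does not govern the primary outcome.
- Name one time point for both the interim and the final primary test.
- Set two-sided limits of about 0.00005, 0.0042, 0.019 and 0.043. If the timing of the looks may vary, use a Lan–DeMets O'Brien–Fleming-type spending function instead.
- Report the final confidence interval at the matching level: 100% − 4.3% = 95.7% for the classical limits.

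This changes wording only. The cost is a slightly stricter final threshold; no more patients are needed. If the named time point is later than 30 days, each look must wait for that follow-up.

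**Interim access.** Replace the access sentence with a rule that a statistician not involved in recruitment or treatment runs the looks and tells the study group only whether the boundary was crossed, with no estimates by arm. The article does not say whether such a person is already available, so one may have to be appointed. The study group also gives up sight of the interim estimates when it decides on stopping. Both changes should be in place before any interim result is seen.
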